### Statistical analysis

2.13

Statistical analysis will be performed after database locking according to a prespecified statistical analysis plan. SPSS version 28.0 will be used for statistical analysis. R software may be used for supplementary analyses when necessary. All statistical tests will be two-sided. A *p* value <0.05 will be considered statistically significant. Effect sizes, 95% confidence intervals, and *p* values will be reported for the primary efficacy results. Except for the primary outcome, analyses of secondary outcomes and follow-up outcomes will be mainly exploratory.

The following analysis sets will be defined in this trial:Full analysis set (FAS): The FAS will include all randomized participants who have at least one post-baseline assessment of the primary outcome. Participants will be analyzed according to their randomized groups. The primary efficacy analysis will be based on the FAS and will follow a modified intention-to-treat principle;Per-protocol set (PPS): The PPS will include participants who complete the main treatment course, have primary outcome data, have no major protocol deviations, and show protocol-compliant adherence. The PPS will be used for sensitivity analysis of the primary outcome;Safety set (SS): The SS will include all participants who receive at least one study intervention and have safety records. Safety analysis will be based on the SS.

Baseline characteristics will be summarized using descriptive statistics. Continuous variables will be presented as the mean ± standard deviation or as the median with interquartile range, depending on data distribution. Categorical variables will be presented as counts and percentages. Baseline balance between the two groups will be described; however, baseline significance testing will not be used as the main criterion for judging the success of randomization.

The primary efficacy endpoint will be the T1 overall VAS score. The primary analysis will use an analysis of covariance model. The T1 VAS score will be used as the dependent variable, group will be included as a fixed factor, and baseline VAS score will be included as a covariate. The adjusted mean difference in T1 VAS score between the two groups will be reported with the 95% confidence interval and *p* value. Descriptive results for the change from baseline to T1 will also be reported. At T1, the proportions of participants achieving a reduction of ≥1.4 cm from baseline in the overall VAS and an overall VAS score of ≤3.0 cm will be summarized by treatment group. Between-group differences will be evaluated using the chi-square test or Fisher’s exact test, as appropriate. Risk ratios and risk differences will be reported with 95% confidence intervals. These responder analyses will be considered supportive and exploratory.

To evaluate treatment trends over time, linear mixed-effects models will be used for continuous repeated-measure outcomes, including the overall VAS, component-specific VAS ratings, SPADI, CMS, and ROM. The models will include group, time, group-by-time interaction, and the corresponding baseline value. Participant will be included as a random effect. Time will be treated as a categorical variable. An unstructured covariance structure will be preferred. If the model does not converge, an appropriate covariance structure will be selected according to model fit indices. The group-by-time interaction will be used to evaluate whether treatment trends differ between the two groups across time points. The between-group difference in the primary outcome at T1 will be the main focus. Between-group differences in changes from baseline at T2 and T3 will also be reported for each outcome.

The component-specific VAS ratings for resting pain, activity-related pain, and nocturnal pain will be analyzed as exploratory secondary outcomes. Between-group differences at T1 will be estimated using analysis of covariance with adjustment for the corresponding baseline pain score. Changes over time will be explored using linear mixed-effects models including group, time, group-by-time interaction, and the corresponding baseline value. Effect estimates and 95% confidence intervals will be reported, and these analyses will be interpreted as exploratory.

Secondary outcomes, including SPADI, CMS, and ROM, will be analyzed using appropriate statistical methods according to variable type and data distribution. Continuous outcomes will be analyzed preferentially using analysis of covariance or linear mixed-effects models. If the data are clearly non-normally distributed, nonparametric tests or appropriate data transformation may be used. Categorical variables will be analyzed using the chi-square test or Fisher’s exact test. Ordinal data will be analyzed using rank-sum tests. Adverse events and SAEs will be described by number, incidence, type, severity, and relationship to the study intervention. Differences in incidence between the two groups will also be compared.

The device-defined output levels recorded after initial stabilization and at the end of each treatment session, the frequency of within-session adjustments, and participant-reported stimulation intensity will be summarized descriptively by treatment group and session. Exploratory analyses may examine associations between recorded stimulation intensity and changes in pain outcomes, with adjustment for treatment group and baseline pain where appropriate. Because stimulation intensity is individually titrated and is not a randomized exposure, these analyses will not be interpreted as evidence of a causal intensity effect.

For missing data, the reason, time point, and type of missingness will first be recorded. In the longitudinal repeated-measures analyses, linear mixed-effects models will use available repeated-measure data under reasonable assumptions about the missing data mechanism. If the proportion of missing data for the primary outcome is high, multiple imputation will be used for sensitivity analysis. The influence of different missing data handling methods on the study conclusions will be compared. Simple last observation carried forward will not be used as the primary method for handling missing data.

Sensitivity analyses will be performed to assess the robustness of the primary findings. These analyses will include an analysis based on the PPS, an analysis excluding participants with major protocol deviations, and analyses addressing rescue analgesic use. The primary analysis will include all available T1 VAS measurements regardless of rescue medication use and will not routinely adjust for post-randomization rescue medication use. The primary analysis will then be repeated after excluding assessments preceded by rescue medication use within 24 h. A further sensitivity analysis will include pre-assessment rescue medication use and the corresponding dose as additional covariates in the analysis of covariance model. The number and proportion of participants using rescue medication, cumulative acetaminophen dose, and number of days of use will be summarized by treatment group. If participants receive prohibited concomitant treatments or experience events that may substantially affect efficacy assessment during the trial, these situations will be documented as protocol deviations and considered in sensitivity analyses.

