### Sample size calculation

2.6

The sample size was calculated using PASS version 2023. Although the primary analysis will use an analysis of covariance model with adjustment for baseline VAS, the sample size was conservatively estimated using a two-sided test for comparing the means of two independent groups, without assuming any efficiency gain from baseline adjustment.

A published randomized controlled trial involving patients with frozen shoulder reported a post-treatment standard deviation of approximately 1.9 cm for the 10-cm VAS in both active treatment groups (12). On this basis, the common standard deviation was conservatively set at 2.0 cm. Considering that the present trial compares two active EA frequency regimens, the smallest between-group difference of interest was set at 1.0 cm, corresponding to a standardized effect size of 0.50. This target between-group mean difference is distinct from the individual-level minimal clinically important difference, which reflects the magnitude of change perceived as beneficial by an individual participant. With a two-sided significance level of 0.05, statistical power of 0.80, and a 1:1 allocation ratio, 64 participants with evaluable primary-outcome data will be required in each group. Allowing for an anticipated attrition rate of 15%, 76 participants will be recruited per group. Therefore, the total planned sample size will be 152 participants.

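### The T1 ANCOVA cannot be run on the full analysis set as defined, and imputation waits for an unspecified level of missingness

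*Protocol article*

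**What the plan says.** All of this is in the protocol article.

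- **Analysis set (section 2.13).** "The FAS will include all randomized participants who have at least one post-baseline assessment of the primary outcome". The primary efficacy analysis is assigned to this set and described as modified intention-to-treat.
- **Visits (section 2.11.1.1).** Overall VAS is measured at baseline and at T1 (week 2), T2 (week 8) and T3 (week 24), so any of three visits can bring a participant into the FAS.
- **Primary model (section 2.13).** "The T1 VAS score will be used as the dependent variable, group will be included as a fixed factor", with baseline VAS as covariate. The sensitivity paragraph adds that every available T1 score enters, whether or not rescue medication was used. No imputation is attached to this model.
- **Imputation (section 2.13).** "If the proportion of missing data for the primary outcome is high, multiple imputation will be used for sensitivity analysis".
- **Sensitivity analyses (section 2.13).** "These analyses will include an analysis based on the PPS, an analysis excluding participants with major protocol deviations", followed by analyses of rescue analgesic use.
- **Mixed model (section 2.13).** A repeated-measures model covering overall VAS is planned without condition. It uses the available data, and its paragraph puts the T1 difference at the centre. A comparison of missing-data methods is also promised.
- **Expected loss (section 2.6).** "Allowing for an anticipated attrition rate of 15%, 76 participants will be recruited per group".

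**The concern.** The named set and the model do not fit each other. Someone seen at T2 but not at T1 belongs to the FAS, yet a one-visit ANCOVA without imputation has no outcome to use for that person. The set really analysed is FAS members with a T1 score, which the protocol does not define.

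A second group falls outside the FAS altogether. T1 is the first assessment after baseline, so a participant who leaves during the two treatment weeks and does not return has no later VAS. Poor relief or discomfort may prompt such exits, and their rate or reasons could differ by stimulation frequency.

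Imputation is the listed tool that could bring both groups back, but it is conditional. The protocol does not say whether it would cover all randomised participants or only the FAS. If only the FAS, the second group stays out, and missingness counted within the FAS would understate the loss that is meant to trigger it.

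At stake is a borderline result. Loss related to pain in one arm would make that arm look better or worse than it is, and the analyses listed as sensitivity checks on the primary result are not aimed at this.

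**Working it through.** **1. The plan's own figures.** Inputs from section 2.6, the first being a per-group number: "With a two-sided significance level of 0.05, statistical power of 0.80, and a 1:1 allocation ratio, 64 participants with evaluable primary-outcome data will be required"; for the spread, "the common standard deviation was conservatively set at 2.0 cm"; for the target, "the smallest between-group difference of interest was set at 1.0 cm, corresponding to a standardized effect size of 0.50".

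- Two-sample t-test, noncentral t, difference 1.0, SD 2.0: power is 0.7952 at 63 per group and 0.8015 at 64. The stated 64 is reproduced.
- Attrition: 64 / (1 − 0.15) = 75.3, rounded up to 76 per group; 2 × 76 = 152. Reproduced.
- Expected without evaluable primary data: 0.15 × 152 = 22.8, about 23. Recruiting 76 to keep 64 allows for 12 per group.

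**2. Who enters the primary ANCOVA.**

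| VAS after baseline | In the FAS? | Used by T1 ANCOVA? | Adds an outcome to the mixed model? |
|---|---|---|---|
| T1, with or without later visits | Yes | Yes | Yes |
| T2 or T3 only | Yes | No | Yes |
| None | No | No | No |

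The FAS and the ANCOVA disagree in the second row. Neither the FAS, the ANCOVA nor the mixed model covers the third.

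**3. Precision with 64 per group** (SD 2.0, no gain from baseline adjustment, as in section 2.6).

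- SE = 2.0 × √(2/64) = 0.354 cm.
- Smallest significant difference = t(0.975; 126 df) × SE = 1.979 × 0.354 = 0.70 cm.

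**4. Size of a possible bias.** Let m be the fraction missing in an arm, and s the amount by which the missing differ from the observed at T1 beyond what baseline VAS explains. The observed mean in that arm is then off by m × s, and the between-arm bias is m₁s₁ − m₂s₂ in absolute size. The documents give no value for s; 1 to 2 cm is an assumption.

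| Scenario | s = 1.0 | s = 1.4 | s = 2.0 |
|---|---|---|---|
| 15% missing per arm, shift in one arm only (0.15 × s) | 0.15 cm | 0.21 cm | 0.30 cm |
| 15% missing per arm, same shift in both (0.15s − 0.15s) | 0 | 0 | 0 |
| 10% vs 20% missing, same shift in both (0.10 × s) | 0.10 cm | 0.14 cm | 0.20 cm |

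**5. Tipping points** (12 of 76 missing per arm, shift in one arm, SE held fixed).

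- Observed difference 0.8 cm: (0.80 − 0.70) / (12/76) ≈ 0.64 cm (unrounded threshold 0.6997).
- Observed difference 1.0 cm: (1.00 − 0.70) / (12/76) ≈ 1.9 cm.

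A result at the target difference needs a large one-arm departure to lose significance. A result of 0.8 cm needs only a modest one.

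**6. What the listed sensitivity analyses do.** The per-protocol set already requires the absence of major deviations, plus completion of the main course, primary-outcome data and adherence. The run that excludes major deviations therefore overlaps with it heavily. Both remove participants. Of the two rescue-medication runs, one removes assessments and the other adds covariates. None varies an assumption about unseen T1 scores.

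**The case against.** A reader might infer that the plan hides its loss of participants, that its missing-data assumption goes entirely unchecked, or that the primary result will be biased. The documents do not support any of these.

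- **Disclosure.** Section 2.13 says that available T1 scores are used and calls the approach modified intention-to-treat. Section 2.6 sizes the trial on evaluable participants after 15% attrition.
- **Existing checks.** The mixed model on overall VAS is unconditional, takes in FAS members who have T2 or T3 but no T1, and is not confined to trends, since its paragraph makes the T1 difference the main interest. A comparison of missing-data methods is promised, reasons for missingness are recorded, and simple last observation carried forward is ruled out as the primary method.
- **Validity.** ANCOVA on observed T1 scores is unbiased if missingness depends only on arm and baseline VAS. The figures above for one-arm shifts are scenarios, not predictions.
- **Detail left to the SAP.** A numerical threshold, the imputation variables and a delta range normally belong in the SAP, which is not shown. Their absence here is no finding.

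These arguments stand and narrow the point. They do not remove it. The FAS wording and the T1 model still disagree in the text as written, and making imputation conditional is itself a stated rule, whatever threshold the SAP sets. The mixed model is not in the list of sensitivity analyses for the primary result, gains nothing from participants with no VAS after baseline, and works under missing at random. A preference for it over ANCOVA as the primary model would be only a preference.

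**Conclusion.** The point holds in a limited form. The primary analysis is assigned to a set on which it cannot be run in full, early leavers are excluded by definition, and imputation is conditional even though about 23 of 152 participants are expected to be lost. The mixed model is a partial check under missing at random, and no stated analysis goes beyond that assumption.

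The possible effect is modest: about 0.15 to 0.30 cm if the missing 15% in one arm only differ by 1 to 2 cm, and zero if missingness and shift are the same in both arms. This rests on an SD of 2.0 cm, no gain from baseline adjustment, and an assumed shift that the documents neither support nor rule out. It would matter for a result near the 0.70 cm threshold and much less for one at 1.0 cm. The sample size is unaffected. This is a cheap improvement, not a flaw that invalidates the design.

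**What to change.** In section 2.13 and the SAP:

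1. Define the primary analysis population as all randomised participants, analysed as randomised.
2. Keep the T1 ANCOVA, but delete the condition on the amount of missing data. Always run it on multiply imputed data for all randomised participants, with arm, baseline VAS, T2 and T3 VAS, rescue use and sessions attended in the imputation model. Name the T1 contrast from the planned mixed model as a sensitivity analysis of the primary result.
3. Add an arm-specific delta (tipping-point) analysis that shifts the imputed T1 scores separately in each arm and reports where the conclusion changes. It can take the place of the run that excludes major protocol deviations, which largely repeats the per-protocol analysis.

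Imputation from baseline and later visits still assumes missing at random, so step 3 is needed as well as step 2, above all for participants with no VAS after baseline.

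Cost: wording changes, a little more analysis work and slightly more complex reporting. No further participants or data are needed, and 64, 76 and 152 stay as they are.

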## Introduction

1

Shoulder periarthritis, also known as frozen shoulder or adhesive capsulitis, is a common shoulder disorder characterized by shoulder pain, restricted active range of motion (AROM) and passive range of motion (PROM), and shoulder-related functional impairment (1). The main pathological processes include capsular inflammation, fibrosis, adhesion, and contracture, which can reduce joint cavity volume and limit shoulder mobility (2).

The disease usually follows a staged clinical course and is commonly described as progressing through a pain-dominant stage, a stiffness stage, and a recovery stage. The pain-dominant stage is mainly characterized by resting pain, nocturnal pain, and activity-related pain, and may also involve a rapid decline in shoulder ROM. These symptoms can substantially affect sleep and daily activities, such as dressing, combing hair, reaching overhead, and shoulder abduction (3). Therefore, treatment at this stage should focus on prompt pain relief, preservation of tolerable shoulder movement, and prevention of persistent functional limitation.

Current conservative treatments for shoulder periarthritis include oral analgesic and anti-inflammatory medications, physical therapy, range-of-motion exercises, and rehabilitation interventions (4). For patients with prominent pain or more severe functional limitation, local corticosteroid injection, hydrodilatation, or other interventional treatments may also be considered (5). These approaches can relieve pain and improve shoulder mobility in the early stage. However, uncertainty remains regarding the optimal timing, treatment combinations, patient responses, and individual suitability of different interventions. Pharmacological and injection-based treatments may also be limited by injection-related discomfort, potential adverse effects, and patient acceptability (6). Therefore, a safe, reproducible, and standardized non-pharmacological treatment strategy is still needed.

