### Inclusion criteria

2.3

Participants must meet all of the following inclusion criteria and none of the exclusion criteria listed in Section 2.4:They meet both the Western medical diagnostic criteria for pain-dominant shoulder periarthritis and the TCM meridian differentiation criteria for the Hand Shaoyang meridian pattern, as described in Section 2.2;They are 30–80 years of age, inclusive, regardless of sex;They have unilateral shoulder pain and restricted shoulder movement, with clear tender points around the affected shoulder;The disease duration is ≥4 weeks and <36 weeks. Because the timing of clinical stage transition varies among patients, eligibility will be determined according to the current clinical presentation rather than disease duration alone. Pain must remain the predominant clinical manifestation, and active resting pain or nocturnal pain must be present, with at least one of these components rated ≥3 cm on a 10-cm VAS at both formal screening and the baseline visit before randomization;The pain score on a 10-cm VAS is >3 at screening;Standard shoulder radiography shows no fracture, dislocation, marked osteoarthritis, or other osseous lesion that could explain the current symptoms, and mandatory diagnostic ultrasonography of the affected shoulder shows no partial-thickness or full-thickness rotator cuff tear or other clinically relevant soft-tissue lesion that could account for the presenting symptoms;They voluntarily agree to participate in the study and sign written informed consent, and are able to complete the treatment, outcome assessments, and follow-up procedures.

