Before any study-related procedure is performed, research staff will provide full information to each candidate participant. This information will include the study purpose, trial procedures, potential benefits and risks, alternative treatment options, data confidentiality measures, the right to withdraw, and protection of medical rights after withdrawal. Candidate participants will be given sufficient time to ask questions and consider participation. Individuals who voluntarily agree to participate will sign written informed consent and receive a unique study identification number. Participants who have signed informed consent and are confirmed as eligible will complete the baseline assessment before randomization. At the baseline visit and before randomization, the study physician will re-evaluate the participant’s current clinical stage. Pain-dominant status will be reconfirmed on the basis of the predominant clinical complaint and the presence and intensity of resting and nocturnal pain. Candidates whose symptoms have transitioned to a stiffness-dominant presentation or who no longer meet the pain-dominant criteria will not be randomized, and the reason for non-enrollment will be recorded in the screening log. Personal information will be used only for the purposes of this study and will be managed in a de-identified manner. Participants may withdraw from the study at any time without penalty. Reasons for withdrawal will be recorded in the screening, enrollment, and follow-up records when available.

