### Randomization and allocation concealment

2.7

Participants who meet the inclusion criteria, meet none of the exclusion criteria, and provide written informed consent will be randomized after the baseline assessment. They will be assigned in a 1:1 ratio to the low-frequency EA group (2 Hz) or the high-frequency EA group (100 Hz). The randomization sequence will be generated by an independent statistician using a computer-generated method. The statistician will not participate in participant recruitment, treatment, outcome assessment, or data analysis. Block randomization will be used. The block size will be determined and kept confidential by the independent statistician.

Allocation concealment will be implemented through a central randomization system. Randomization will be performed only after eligibility confirmation, informed consent, and baseline assessment have been completed. The allocation result will be available only to the treating acupuncturist responsible for delivering the intervention. The treating acupuncturist will not participate in outcome assessment or data analysis. Investigators, outcome assessors, data managers, and statistical analysts will have no access to the randomization sequence or the complete allocation list before database locking. The randomization sequence, allocation records, and system operation logs will be stored by independent personnel.

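### The outcome models omit disease duration, which is known for everyone at entry and ranges from 4 to under 36 weeks; adding it could gain a little precision at almost no cost

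*Protocol article*

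**What the plan says.** **Entry window.** Section 2.3 states: "The disease duration is ≥4 weeks and <36 weeks". It adds that "eligibility will be determined according to the current clinical presentation rather than disease duration alone".

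**Natural course.** The Introduction says that the disease is "commonly described as progressing through a pain-dominant stage, a stiffness stage, and a recovery stage".

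**Control of stage.** Sections 2.2.1 and 2.3 require pain to predominate, with resting or nocturnal pain of at least 3 cm at both screening and baseline. Section 2.5 repeats the stage check before randomisation: "Candidates whose symptoms have transitioned to a stiffness-dominant presentation or who no longer meet the pain-dominant criteria will not be randomized".

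**Randomisation.** Section 2.7 gives a 1:1 ratio and says "Block randomization will be used". It names no stratification factor.

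**Models.** Section 2.13 lists the model terms. The T1 ANCOVA has group and baseline VAS. For the mixed models of overall and component VAS, SPADI, CMS and ROM: "The models will include group, time, group-by-time interaction, and the corresponding baseline value". None of the listed sensitivity analyses uses disease duration.

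**Status of the analyses.** T1, at 2 weeks, is the primary time point. Section 2.13 calls the secondary and follow-up analyses mainly exploratory.

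**The concern.** Two people can both be pain-dominant at baseline with the same VAS, one about 5 weeks from onset and the other about 35. The entry rules treat them alike, and at T0 they are alike in stage. They need not follow the same course afterwards. By T3, 24 weeks after treatment starts, the window of time since onset is roughly 28 to 60 weeks (4 + 24 to 36 + 24). In a disease that moves from pain to stiffness to recovery, part of the spread in T2 and T3 scores may reflect time since onset rather than treatment.

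Duration has to be established for every participant, because eligibility depends on it. Section 2.13 names the covariates explicitly and duration is not among them, so the point concerns a stated choice rather than a detail left open.

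What is at stake is precision. The trial compares two active regimens and estimates only the difference between them. The Introduction also expects it to inform on effects sustained during follow-up, for which no separate power calculation is given. If duration predicts outcome beyond the baseline score, adjusting for it narrows these comparisons without any extra data.

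**Working it through.** **Inputs from Section 2.6.** SD 2.0 cm; target difference 1.0 cm; two-sided alpha 0.05; power 0.80; 1:1 allocation; 64 evaluable per group; 15% attrition; 76 recruited per group. No gain from baseline adjustment is assumed.

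**Reproducing the plan's figure.** A two-sample t-test with d = 1.0/2.0 = 0.50 needs 63.77 per group, so 64, with power 0.801. Attrition: 64/(1 − 0.15) = 75.3, so 76 per group and 152 in total. The stated numbers are correct.

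**Effect of adding duration.** Let R² be the share of outcome variance that duration explains. The documents give no value, so R² is an assumption shown over a range.

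- Residual SD = 2.0 × √(1 − R²)
- 95% CI half-width = 1.98 × residual SD × √(2/64)
- Power from the t-test with d = 1.0/residual SD and 64 per group

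| R² (assumed) | Residual SD (cm) | Power at 64 per group | 95% CI half-width (cm) |
|---|---|---|---|
| 0 | 2.000 | 0.801 | 0.70 |
| 0.01 | 1.990 | 0.805 | 0.70 |
| 0.05 | 1.949 | 0.821 | 0.68 |
| 0.10 | 1.897 | 0.841 | 0.66 |

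The gain is about 0.4, 2 and 4 percentage points of power.

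**On top of the planned baseline adjustment.** The table starts from the unadjusted SD, as the sample size does. If baseline VAS correlates 0.5 with T1 VAS (assumed), power at 64 per group is already 0.900. It becomes 0.914 or 0.927 if duration explains 5% or 10% of the remaining variance. At a correlation of 0.3 the sequence is 0.837, 0.855, 0.873. The pattern is the same and the gain stays small.

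**Chance imbalance.** With 64 per group, the standardised difference in mean duration between arms lies within ±1.96 × √(2/64) = ±0.35 SD in 95% of randomisations. An imbalance at that limit moves the unadjusted VAS difference by √R² × 2.0 × 0.346:

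- R² = 0.01: 0.07 cm
- R² = 0.05: about 0.15 cm
- R² = 0.10: 0.22 cm

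These shifts are part of the sampling variation that the 0.70 cm half-width already covers. They are not an error in addition to it.

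**The case against.** The strongest case against is that nothing here is wrong. ANCOVA on the baseline score is standard and valid, and further covariates or supportive adjusted analyses could be added in the analysis plan, which is not shown. The protocol also controls stage directly, with two checks before randomisation, and gives its reason: "Because the timing of clinical stage transition varies among patients, eligibility will be determined according to the current clinical presentation rather than disease duration alone". By that reasoning duration is an imperfect proxy for stage. A single linear slope may also fit a staged course poorly.

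Much of this stands, and it sets the limits of the point. It does not remove it. The stage checks align participants at T0 and say nothing about how soon each moves on. Section 2.3 still bounds duration at both ends, so the protocol itself treats duration as relevant. An imperfect predictor can still reduce residual variance.

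Three stronger readings may tempt a reader, and the documents support none of them.

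- **That the comparison is biased, or that nothing balances duration.** Randomisation balances it in expectation, and the confidence interval already allows for chance imbalance. Recovery common to both arms cancels in the contrast. Only recovery that varies with duration, beyond what the baseline score captures, adds noise.
- **That the loss is large.** This needs a steep slope of VAS on duration. A slope of 0.10 cm per week, for example, implies a 3.2 cm gap across the 32-week window at equal baseline pain, over three times the target difference. No figure in the documents supports such a slope.
- **That the loss is greatest at T2 and T3.** This is plausible for a staged disease followed to 24 weeks, but no figure in the documents shows it, and those analyses are mainly exploratory.

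**Conclusion.** The point holds as a minor matter of efficiency. The stated models leave out a baseline variable that is available for everyone and may be prognostic. The consequence is some lost precision, without bias and without an invalid test. The planned 80% power at T1 is unaffected, because the sample size rests on the unadjusted SD of 2.0 cm; 152 participants remain sufficient on the plan's own assumptions.

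The size depends wholly on an assumed R². Between 1% and 10%, the gain in power at 64 per arm runs from under half a percentage point to about four, and the CI half-width shrinks by at most about 0.04 cm. If duration carries no information beyond the baseline score, the gain is nil and the cost negligible.

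**What to change.** Before unblinding, and in the analysis plan that Section 2.14 says will be finalised before database lock:

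- add baseline disease duration (weeks, continuous) as a covariate in the T1 ANCOVA, beside group and baseline VAS;
- add duration and a duration-by-time term to the mixed models for VAS, SPADI, CMS and ROM, so that its effect may differ at T1, T2 and T3.

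The ANCOVA loses one degree of freedom. Each mixed model loses three: one for duration and two for its interaction with the three post-baseline visits. Randomisation, sample size, visits and data collection do not change. Fixing the term now also avoids a decision to adjust taken only after an imbalance in duration has been seen.
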